### Mediators and moderators

The mediation analysis will be conducted using the PROCESS macro-Version 3.5 developed by Andrew F. Hayes. This research uses a single mediator model to examine the total, direct, and indirect effects. The independent variables will be the groups in the RCT study (ACT intervention group and control group). At the same time, the dependent outcomes will be the change scores of illness cognition and QoL from pre-treatment to post-assessment. The change score is chosen as the dependent variable to assess the improvement of scores between pre-and post-treatment. Proposed mediator variables include psychological inflexibilities, anxiety, depression and social support. PROCESS will be used to validate the mediating effect of psychological inflexibility and disease cognition on the relationship between the ACT intervention and QoL. The Bootstrap program will confirm the direct and indirect effects. Additionally, social support will be introduced as a moderating variable in the coping path to create a final model that verifies the overall mediating product.

## Safety monitoring

Ensuring participant safety is of the utmost importance throughout the study. Therapists delivering the ACT intervention will undergo training to promptly identify and address any potential adverse events or reactions that may arise during therapy sessions. In the event of an adverse incident, participants will have the option to withdraw from the research. Participants will be actively encouraged to report any concerns or negative experiences related to the intervention. Any negative medical development affecting a trial participant unrelated to the treatment intervention is considered an adverse event (AE). Any unwelcome or unexpected indications, symptoms, or transient diseases are included, regardless of how they relate to the experimental intervention.

Participants are strongly advised to regularly contact the research team by phone and quickly report any adverse events (AEs) they may encounter. Participants will get a study card with the research team’s contact details. If an adverse event (AE) does take place, it will be noted in the “Adverse Event” part of the case report form (CRF) for the research, and, if required, a thorough adverse event report will be created. The name of the AE, its start and recovery dates, intensity, relevance to the intervention under study, measures done in response to the intervention, any therapy given, and the result (whether resolved or continuing) are all included in these reports. At Universiti Sains Malaysia, the Human Research Ethics Committee will be informed of severe adverse occurrences. The Common Terminology Criteria for Adverse Events (CTCAE) version 5.0 will be used to monitor the occurrence of adverse effects among participants.

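### The sentence defining an adverse event limits it to events unrelated to the intervention, contradicting the next sentence and the report's relatedness item

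*Protocol article*

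**What the plan says.** All the relevant text is in the Safety monitoring section of the protocol article. No other section defines an adverse event.

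- Definition: "Any negative medical development affecting a trial participant unrelated to the treatment intervention is considered an adverse event (AE".
- Sentence immediately after it: "Any unwelcome or unexpected indications, symptoms, or transient diseases are included, regardless of how they relate to the experimental intervention".
- Content of an adverse event report: among other items, "relevance to the intervention under study".
- Training: "Therapists delivering the ACT intervention will undergo training to promptly identify and address any potential adverse events or reactions".
- Participant reporting: "Participants will be actively encouraged to report any concerns or negative experiences related to the intervention".
- Grading: CTCAE version 5.0 "will be used to monitor the occurrence of adverse effects among participants".

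An event that counts as an adverse event is entered in the dedicated part of the case report form, with a fuller report where required.

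**The concern.** An adverse event is normally recorded first and judged for relatedness afterwards. The first sentence here builds the judgement into the definition, and in the wrong direction: an event thought to be caused by the sessions would not qualify. The following sentence says relation does not matter, at least for some kinds of event, and the report form asks for relation as though it could vary.

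The definition decides what is entered in the adverse event part of the case report form. Two people applying different sentences to the same event could reach different decisions, so the event count and the split by relatedness would depend on which sentence each had in mind. The article also says that the findings are meant to inform clinical practice and possible use of ACT, so readers will want a harm count with a clear meaning.

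**Working it through.** No arithmetic applies. The plan gives no figure on this point, and sample size, power, effect size and dropout do not enter it. The check is a reading of the section against itself.

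**Step 1. Does the first sentence restrict?** Yes. It attaches the lack of relation to the events being defined, so on its own it admits only unrelated events.

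**Step 2. What does the second sentence add?** It admits three kinds of event (signs, symptoms and transient diseases) whatever their relation. It can be read in two ways:

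- As a gloss on the first sentence, listing examples of what that sentence covers. The two then contradict each other directly.
- As an extension that adds these events to those already admitted. The definition is then the union of the two sentences.

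The text does not say which is meant.

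**Step 3. Classify events under the more generous reading (the union).**

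| Event | First sentence | Second sentence | Outcome |
|---|---|---|---|
| Unrelated; sign, symptom or transient disease | admits | admits | adverse event |
| Unrelated; any other negative medical development | admits | silent | adverse event |
| Related; sign, symptom or transient disease | excludes | admits | adverse event, if the second sentence prevails |
| Related; any other negative medical development | excludes | silent | not clearly an adverse event |

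The third row is the contradiction. The fourth is the residual gap. A lasting condition, or a worsening of an existing illness, judged to be related to the intervention would fall there unless staff recorded it through its symptoms. Because the second sentence limits diseases to transient ones, the diseases it leaves out are the longer-lasting ones.

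**Step 4. Compare with the rest of the section.** The relatedness item could take only one value if the first sentence governed, so it presupposes that related events can be adverse events. Training therapists to notice events or reactions arising in sessions, and asking participants for negative experiences connected with the intervention, both look for events that the first sentence excludes. Using CTCAE for adverse effects points the same way. The restricting phrase in the first sentence stands alone against all of these.

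**Step 5. Is there another explanation?** The sentence is complete, current text. It is not redacted, is not a damaged table and is not part of a change log. No definition elsewhere in the article overrides it.

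**The case against.** The strongest case on the other side is that this is a drafting slip for a phrase such as *whether or not related*, and that nobody reading the whole section would be misled. Most of that stands. The second sentence, the relatedness item, the therapist training and the request to participants all show that related events are meant to be captured, and they would probably be recorded in practice.

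A reader might infer something stronger: that the protocol excludes the therapy-related harms it sets out to detect, so that the reported harm rate in the ACT arm will be too low. The documents do not support this. Distress made worse by a session, the most obvious harm of a talking therapy, is an unwelcome symptom, and the second sentence includes it expressly; leaving it out would breach the text. An understated harm rate would require staff to apply the first sentence and ignore the second, and nothing suggests they will. Nor is a harm rate among the listed outcomes or planned analyses.

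It can also be said that the gap is thin, since harms from four one-hour sessions would mostly show as symptoms, and that the full protocol or the form's instructions may be worded correctly. Both are fair, and they limit the weight of the point. They do not remove it: the published article chose to state a definition, and the one it states is wrong as written.

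**Conclusion.** The point holds as an internal contradiction in an operational safety rule, with a narrow residual gap. The first sentence restricts adverse events to unrelated ones; the next sentence and the relatedness item assume otherwise; and staff are not told which governs. Related events that are signs, symptoms or transient diseases are captured when the section is read as a whole. Related events of any other kind are excluded by the first sentence and not clearly restored.

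The size cannot be put as a number. The documents give no expected event rate, and the effect depends on which sentence staff apply. Randomisation, sample size, the primary outcome and the efficacy analyses are untouched. It should be corrected because it governs what is recorded as harm, but it is no threat to the main result.

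Confidence is high on the wording conflict and lower on any practical consequence. The conclusion assumes that the article's wording is what staff follow. If a fuller protocol or form instruction already gives one consistent definition, only the published text needs correcting.

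**What to change.** Merge the two sentences into one definition. In the first sentence, replace the phrase that limits events to unrelated ones with *whether or not considered related to the study intervention*. Fold the signs, symptoms and transient diseases of the second sentence in as examples, so that they no longer act as a separate and narrower rule. State that the definition applies in both arms. The first sentence already speaks of any trial participant, and the control group also attends four sessions with the same therapists, so this clarifies the scope without widening it. Keep relatedness as a separately recorded attribute of each event, as the report content already provides.

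The cost is one sentence in the protocol, with matching wording in any instructions for completing the case report form. A few more events may be recorded. Sample size, assessment schedule, analysis and the management of participants do not change.

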### Blinding

Participants will be unaware of the study’s randomization into the designated groups, which will be carried out by a research assistant who is not otherwise involved. As a result, participants will not be informed of the group to which they are allocated.

Additionally, to minimize bias, the ACT intervention group and the control group will receive a 4-session program (with one hour per session, one session per week for 4 weeks). Participants in the control group will also receive equal attention (attentive listening) and time from the professional figure administering the program with non-therapeutic intervention(the participants in the control group are given equal duration of the session, number of sessions, duration of intervention and attended by the same therapists who conducted the ACT group. The participants will also be attended to with active listening by the therapists in the control group).

To maintain blinding throughout the study, the researchers will be blinded to participants’ randomized assignments into the groups. This process will be carried out by a research assistant who is not involved in the study. Additionally, data collection for this study will be conducted by the same research assistant, ensuring impartiality. The research assistant will remain unknown to the study’s hypotheses. Furthermore, data analysis for the study will be performed by statisticians who are not involved. The statistician will utilize a statistical analysis plan to conduct data analysis before the final unblinding of the data lock.

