### Control group

The control group participants will receive treatment as usual, including nonspecific and nontherapeutic approaches such as providing psychological understanding, identifying current problems, and practising deep breathing exercises. They will receive the same amount of time and attention from the same therapist as the intervention groups and participate in a one-session weekly program for four weeks.

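### Adverse events are collected mainly through participants phoning in or volunteering reports, with no scheduled AE question described in either arm, so events are likely to be under-counted and could be counted unequally

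*Protocol article*

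**What the plan says.** All of the AE procedure is in the Safety monitoring section of the protocol article. It describes four elements:

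- Reporting by telephone, supported by a study card with the team's contact details: "Participants are strongly advised to regularly contact the research team by phone and quickly report any adverse events (AEs) they may encounter".
- Encouragement to volunteer problems: "Participants will be actively encouraged to report any concerns or negative experiences related to the intervention".
- Detection by therapists: "Therapists delivering the ACT intervention will undergo training to promptly identify and address any potential adverse events or reactions that may arise during therapy sessions".
- A grading system: "The Common Terminology Criteria for Adverse Events (CTCAE) version 5.0 will be used to monitor the occurrence of adverse effects among participants".

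Reported events go on an AE part of the case report form (CRF), and severe ones are notified to the ethics committee.

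Two other sections bear on the point. Under Blinding, control participants are "attended by the same therapists who conducted the ACT group". Under Control group, "They will receive the same amount of time and attention from the same therapist as the intervention groups", and they "participate in a one-session weekly program for four weeks". The Procedure section places questionnaire assessments before the intervention, directly after it and three months later, and mentions no AE enquiry at any of them.

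**The concern.** A method that waits for the participant to call records the events of those who choose to call. The participants are on active cancer treatment, so new symptoms are plausible in both arms, and many may not seem worth a telephone call. Distress provoked by a psychological session may be even less likely to be volunteered.

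The detection duty adds a second difficulty. It is the only AE task given to staff who meet participants in the sessions, and it is attached by name to ACT delivery. The control arm also has four weekly hours with a therapist, and nothing is said about looking for events there.

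At stake is whether the trial can say anything reliable about harms. The article hopes to inform practice and the possible inclusion of ACT in routine care. A low AE count obtained mainly by spontaneous reporting would be weak support for that.

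**Working it through.** The article contains no AE rate, capture rate or harms analysis, so there is no figure to reproduce. The check is a reading of the text, followed by an illustration on assumed values.

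**Step 1. Each stated route, and what it covers**

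| Route | Arms covered | Who starts it | Tied to a scheduled contact? |
|---|---|---|---|
| Phone call, study card | Both | Participant | No |
| Encouragement to report | All participants, but about experiences linked to the intervention | Participant | No |
| Therapist detection | Worded for therapists delivering ACT | Therapist | Sessions, with no set question |
| CTCAE v5.0 | Both | Not stated | No |

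CTCAE is a grading vocabulary. The text gives it no schedule, question or responsible person, so it adds no described means of finding an event.

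**Step 2. Contacts at which a question could be asked.** There are four weekly sessions, then the post-intervention and three-month assessments: 4 + 2 = 6 contacts per participant. None carries a described AE question. After the fourth session no further therapist contact is described, which leaves volunteered reports until the follow-up assessment. The Objective section instead lists assessments at 4 weeks, 6 months and 12 months. On that schedule the count would be 4 + 3 = 7 contacts, and the stretch without sessions would be longer. The two schedules need reconciling in any case.

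**Step 3. Are the arms treated differently?** The detection sentence names ACT therapists. Blinding and Control group put those same people in control sessions for equal time. Training travels with the person, so equal contact and equal training are supported. An equal detection task in control sessions is neither stated nor excluded. The sentence speaks of therapy sessions, while the control programme is described as non-therapeutic, so it can be read either way.

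**Step 4. What under-capture and unequal capture would each do.** Let p be the true AE risk, equal in both arms, and s the share of events captured, with no false reports. Observed risk = p × s. Observed risk ratio = (p × s in ACT) / (p × s in control) = s in ACT / s in control. With p assumed to be 20%:

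| Capture, ACT / control | Observed, ACT / control | Difference | Risk ratio |
|---|---|---|---|
| 90% / 90% | 18% / 18% | 0 | 1.0 |
| 60% / 60% | 12% / 12% | 0 | 1.0 |
| 90% / 60% | 18% / 12% | 6 points | 1.5 |
| 90% / 30% | 18% / 6% | 12 points | 3.0 |

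With p of 10% or 40% the ratios are unchanged. The differences in the last two rows become 3 and 6 points at 10%, and 12 and 24 points at 40%. Equal capture of 60% loses 40% of events without creating a false difference; a false difference needs unequal capture. These rates are assumptions, not estimates. The table shows what would follow from unequal capture and is no evidence that it will occur.

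**The case against.** The strongest objection is to a reading that is tempting here: that AEs are found only by phone and in ACT sessions, that ascertainment is unequal by design, and that a comparison of harms would be biased. The document does not support it. Encouragement to report and CTCAE monitoring are stated as well. The phone route, study card, CRF page and CTCAE have no arm restriction. The same trained therapists see controls for the same time. The statistical analysis sections cover the questionnaire outcomes and plan no between-arm comparison of harms that could be biased. In addition, anxiety and depression are measured with the same scale in both arms, so worsening distress would be partly visible even if never reported as an AE. All of this stands.

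A further objection is that a journal article condenses a fuller protocol, and that the wording of an AE question belongs there or in the CRF; the schedule figure is also not shown. This stands in part. The missing script alone would be no finding. But the article does state a method, and that method is mainly participant-initiated with a detection duty worded for one arm. If the full protocol already has a scheduled enquiry in both arms, the published text should say so.

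**Conclusion.** The point holds as a modest one. Followed as written, the procedure relies mainly on participants coming forward, and under-counting of AEs is likely. How much cannot be derived from the article.

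Unequal counting between arms is a possibility. It rests on three features: a detection sentence that names ACT therapists, encouragement tied to the intervention, and therapists who know which programme they are delivering. Shared therapists and equal session time count against it, and nothing in the text establishes it. A reader should not conclude from this section that a harms comparison is already biased.

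The conclusion assumes that the figures not shown and any fuller protocol contain no scheduled AE enquiry. If they do, what remains is to bring the article into line.

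**What to change.** - Ask one identical open question in both arms, for example whether any new or worsening problem has arisen since the last contact. Ask it at each of the four sessions and at each post-baseline assessment, and record the answer on the existing AE page of the CRF. Where questionnaires are completed online, which the Outcomes section allows, put the question in the online form.
- State that AE training and detection by therapists apply to control sessions as well as ACT sessions.
- Keep the phone card as a supplement.
- Report AEs by arm, from the first session to the final assessment.
- While revising the section, reconcile its AE definition. One sentence limits AEs to events not related to the intervention, and the next includes events whatever their relation to it. The answers cannot be classified consistently until this is settled.

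The cost is one question at contacts that already take place (six per participant on the Procedure schedule) and a wording change to training already planned. No visit is added. The downside is more minor events to record and grade, many of them due to cancer treatment.

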## Data sharing and dissemination

Authorship eligibility will be determined by suggestions made by the International Committee of Medical Journal Editors. Access to the study’s files for data analysis or publishing is only allowed for the study’s corresponding author and co-authors. The study findings will be disseminated through various channels to maximize their impact and reach. Data collected from the survey will be protected and stored securely. Only aggregated and de-identified data will be reported in publications, ensuring the anonymity of participants. The results will be analyzed and prepared for publication in peer-reviewed journals, and presentations will be made at scientific conferences and meetings relevant to breast cancer, psycho-oncology, and psychological interventions. In addition, efforts will be made to communicate the findings to appropriate stakeholders, including healthcare professionals, patient advocacy groups, and policymakers, to inform clinical practice and potential implementation of ACT interventions for breast cancer patients. The researchers of this study all state that they have no conflicting financial or other interests.

## Limitations and future research

It is important to recognise certain potential limitations of the study. Firstly, the study design relies on self-report measures, which are susceptible to response biases. To address this, participants will be assured of the confidentiality and anonymity of their responses to encourage honest reporting. Secondly, the study will be conducted in Eastern Malaysia and may not fully capture the diverse experiences of breast cancer patients nationwide. Future research should replicate the findings in larger, more diverse populations to enhance generalizability. Third, the sample size may be relatively small. However, it is deemed sufficient upon sample size calculation, considering the heterogeneity of the participants and the self-reported measuring tools used in the study, which may further affect the level of generalisation. Finally, this study did not assess the survival rate of breast cancer patients as an outcome.

In summary, this study is committed to maintaining the highest ethical standards and prioritizing participant safety while examining the impact of ACT on disease acceptance among breast cancer patients.

